Two studies showed that a significant increase in TReg cells from month 6 after rituximab infusion is associated with clinical response (33, 34). This increase is associated with IL-35 increase and PLA2R1-Ab decrease (33). IL-35 is an inhibitory cytokine that contribute to regulatory T-cell function. These results must be confirmed in large cohort to understand mechanisms of rituximab resistance and proposed new strategies (35). We propose to confirm these results in an ancillary study.

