## 2.2 Secondary Objectives

The following objectives are to compare between a personalized treatment of iMN driven by anti-PLA2R1 antibody epitope profiles and the GEMRITUX therapeutic protocol:

1. Complete clinical remissions at M6, M9, M12, M18, M24
2. Partial clinical remission at M6, M9, M12, M18, M24
3. Immunological remissions at M6, M9, M12, M18, M24
4. Proteinuria and albuminuria at M6, M9, M12, M18, M24
5. Changes in proteinuria and albuminuria from baseline at M6, M9, M12, M18, M24
6. Serum creatinine and estimated glomerular filtration rate (eGFR) at M6, M9, M12, M18
7. Changes in serum creatinine and eGFR from baseline at M6, M9, M12 and M18
8. PLA2R1-Ab titers at M6, M9, M12, M18 and M24
9. Recording all AEs/SAEs during study follow-up, 24 months

The following objectives aim to study risk factors for remission or relapse:

10. To determine risk factors for remission (immunological and clinical, partial or complete) at M12 in patients pooled from the two arms
11. To determine risk factors for relapse (between M12 and M24) in patient responders at M12, pooled from the two arms

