## 3. Evaluation criteria

### Principal evaluation criteria:

Clinical remission will be defined as a composite criterion combining (KDIGO definitions):

- Complete clinical remission: urinary protein/creatinine ratio (UPCR)<0.3 g/g in spot morning urine samples and Normal serum albumin and eGFR > 60 ml/min/1.73 m^2

- Partial clinical remission: UPCR < 3.5 g/g with a decrease greater than 50% from baseline and improvement or normalization of the serum albumin concentration and increase of serum creatinine lower than 20%

Secondary evaluation criteria:

1. Complete clinical remission as defined above
2. Partial clinical remission as defined above
3. Immunological remission: full PLA2R1 depletion measured by ELISA (titer<14RU/ml)
4. Proteinuria and albuminuria are measured on urine sample (proteinuria-to-creatinine ratio or albuminuria-to-creatinine ratio g/g) or collected during one day (g per day)
5. Change in proteinuria are measured in percentage change in proteinuria from baseline to M6, M9, M12, M18, M24
6. Serum creatinine is measured in blood sample in  $\mu\text{mol/l}$  and eGFR using the CKD-EPI formula.
7. Change in serum creatinine and eGFR are measured in percentage change from baseline to M6, M9, M12, M18, M24
8. PLA2R1-Ab titer are measured by ELISA in RU/ml
9. Severe infections are defined as infections that led to hospitalization during study follow-up
10. Remission will be defined as already stated. Patients from both groups will be analysed jointly. The following risk factors will be studied in this analysis:
  - Lymphocyte counts: B cells (CD19, transitional, mature and memory) and T cells (CD3, CD4, CD8 and TReg) measured in blood sample at J0, M3, M6, post-rituximab infusion
  - Serum level of cytokines (pg/ml) measured in blood sample at J0, and after first remission (or M24 if no remission)
  - Residual serum rituximab levels ( $\mu\text{g/ml}$ ) measured in blood sample at M3 post-rituximab infusion using ELISA
  - Neutralizing anti-rituximab antibodies (ng/ml) measured in blood sample at M3 and M6 post-rituximab infusion
11. Responders are patients entered in partial or complete remission at M12. Relapse is defined by an increased proteinuria > 3.5 g/g after remission at M12. Patients from both groups will be analysed jointly. The risk factors studied will be the same as above measured at J0, M3, M6, M9 and M12 post-rituximab infusion.

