### 8.5 Definition of patient data to be gathered and directly entered in the patient electronic case file, which will be considered the source data:

#### Inclusion/Randomization visit (M0)

- Consultation date
- Demographic data: date of birth, sex
- History of MN
- Paraclinic tests to eliminate secondary MN when performed: body scan, anti-nuclear antibodies, HBV, HCV serologies
- Current treatment
- Clinical examination: weight, height, blood pressure, edema
- Blood sample: urea, creatinine, electrolytes (Na, K, Cl, HCO3), protein, albumin, full blood count
- Urine collection on a spot morning sample: protein, albumin, urea, creatinine
- Centralized assays : for both groups,

- 2 dry tubes of 5 ml of blood and 2 EDTA tubes of 3 ml of blood will be shipped to Nice at room temperature for PLA2R1-Ab, epitope profile determination, anti-rituximab antibodies, B and T cells counts (see manual lab),
  - 1 lithium heparin tube of 4 ml of blood for cytokine profile analysis will be shipped to Nice at 4°C.
- 
- Start vaccination (pneumococcal and influenza vaccine) between randomization and first injection at the latest.
  - In the GEMRITUX arm, plan M3 in 3 months +/-15days and hand out a prescription to the patient for blood and urine analyses\* (results needed for the next visit as per routine follow-up);
  - In the Personalized Treatment arm, plan next visit according to the epitope profile results provided by the central lab within 48 hours:
    - Restricted anti-CysR activity: 6-month symptomatic treatment as in GEMRITUX arm - > plan M3 visit in 3 months +/-15 days and hand out a prescription to the patient for blood and urine analyses\* (results needed for the next visit as per routine follow-up);
    - Anti-CTLD1/7 activity: plan two 1g rituximab infusions at 2-week interval +/-2 days. The treatment should start between 5 and 14 days after randomization. After the first injection, plan M3 visit in 3 months +/-15 days and hand out a prescription to the patient for blood and urine analyses\* (results needed for the next visit as per routine follow-up)

\* Blood sample: urea, creatinine, electrolytes (sodium, potassium, chloride, bicarbonate), protein, albumin, full blood count.

Spot morning urine sample: protein, albumin, urea, creatinine.

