### **At the first remission**

One tube of lithium heparin of 4 ml of blood (for cytokine profile analysis) will be performed at the first remission and shipped to Nice at 4°C. If the sample cannot be collected during the visit when the remission is first confirmed, it must be collected at the following visit or at M24 for all patients that have not entered remission until the end of study.

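### The second cytokine sample is timed by remission itself, so it should not be listed as a risk factor for remission at M12; only the J0 level can serve

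*Protocol*

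**What the plan says.** Objective 10 (protocol, Section 2.2) is "To determine risk factors for remission (immunological and clinical, partial or complete) at M12 in patients pooled from the two arms". Section 3, secondary criterion 10, puts this into practice: "The following risk factors will be studied in this analysis", followed by four items. Three have visits fixed relative to infusion: lymphocyte counts at J0, M3 and M6; residual rituximab at M3; anti-rituximab antibodies at M3 and M6. The fourth is the exception: "Serum level of cytokines (pg/ml) measured in blood sample at J0, and after first remission (or M24 if no remission").

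Section 8.5 gives the collection rules. At M0, "1 lithium heparin tube of 4 ml of blood for cytokine profile analysis will be shipped to Nice at 4°C". Later, under the heading on first remission, "One tube of lithium heparin of 4 ml of blood (for cytokine profile analysis) will be performed at the first remission"; if that visit is missed, "it must be collected at the following visit or at M24 for all patients that have not entered remission until the end of study". The cytokine row of the schedule of assessments agrees: M0, then first remission, with no fixed visit after M0.

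For relapse between M12 and M24 in M12 responders, criterion 11 says: "The risk factors studied will be the same as above measured at J0, M3, M6, M9 and M12 post-rituximab infusion".

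**The concern.** A risk factor for an outcome has to be measured before the outcome, at a time that does not depend on it. The second cytokine value fails the second condition by design and, for most patients, the first as well. Remitters contribute a value taken while in remission, often within the first year. Patients without remission by M12 contribute a value taken 6 or 12 months after the outcome was recorded. A cytokine that drifts over time, changes with time since rituximab, or normalises when the disease settles would then separate the two groups even if it had no influence on who remits.

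At stake is the reading of one secondary, pooled-arm objective: a marker could be reported as predicting remission when it only reflects remission or the calendar. An analysis plan can restrict the analysis to J0, but it cannot create a fixed-time sample that was never drawn, so the protocol text is the place to settle this.

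**Working it through.** **1. Sampling time by outcome.** Applying the Section 8.5 rule to the M12 outcome:

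| Patient's course | Status at M12 | Second cytokine sample |
|---|---|---|
| First remission by M12, maintained | remitter | at that remission visit, or the next visit if missed |
| First remission at M18 | non-remitter | M18, or M24 if missed (6 to 12 months after the outcome) |
| Never in remission | non-remitter | M24 (12 months after the outcome) |
| Remission at, say, M6, relapse by M12 | non-remitter | M6, or the next visit if missed |

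No row gives a common time before the outcome. The last row shows that first remission and M12 status overlap without being identical; the timing is still set by remission.

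**2. Size of the timing gap (assumed visit mix).** The protocol gives no distribution of first-remission visits, so one is assumed. Personalised arm: M3/M6/M9/M12 with probabilities 0.25/0.40/0.20/0.15. Control arm: M6/M9/M12 with 0.35/0.25/0.40. M12 non-remitters: 30% at M18, 70% at M24. Remission rates of 80% and 45% and the total of 64 patients come from Section 7.

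- Remitters: 32 × 0.80 = 25.6 and 32 × 0.45 = 14.4, together 40; non-remitters 24.
- Mean sampling month, personalised remitters: 3(0.25) + 6(0.40) + 9(0.20) + 12(0.15) = 6.75. Control remitters: 6(0.35) + 9(0.25) + 12(0.40) = 9.15.
- All remitters: (25.6 × 6.75 + 14.4 × 9.15)/40 = 7.6 months.
- Non-remitters: 18(0.30) + 24(0.70) = 22.2 months.
- Gap: 22.2 − 7.6 = 14.6 months.

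**3. False-positive rate.** Take a cytokine with SD 1, unrelated to remission, drifting by d SD over 24 months, compared between M12 remitters and non-remitters by a two-sided 5% t-test. The expected difference is d × 14.6/24 = 0.608d. The standard error is √(1/40 + 1/24) = 0.258. The normal approximation to the rejection rate, against simulation (4,000 runs per setting):

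| Drift d over 24 months | 0.608d/0.258 | Normal approximation | Simulation |
|---|---|---|---|
| 0 | 0 | 5% | about 5% |
| 0.25 SD | 0.59 | 9% | 9% |
| 0.5 SD | 1.18 | 22% | 21% |
| 1.0 SD | 2.36 | 65% | 61% to 63% |

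**4. Sensitivity.**
- A different assumed setting (58 patients, 62.5% remission, remitters spread evenly over M6/M9/M12, 25% of non-remitters at M18 and the rest at M24) gives a gap of 13.5 months. The rates are 5%, 17%, 29% and 67% at drifts of 0, 0.02, 0.03 and 0.05 SD per month (0, 0.48, 0.72 and 1.2 SD over 24 months). The J0 sample stays near 5% throughout.
- If 20% of M12 non-remitters had remitted at M6 and relapsed, the gap in step 2 becomes 0.8 × 22.2 + 0.2 × 6 − 7.6 = 11.4 months. The simulated rates at 0.25, 0.5 and 1.0 SD fall to about 8%, 15% and 42%.

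These figures cover drift with time only. Any effect of remission on the cytokine would be added.

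**5. Criterion 11 against the schedule.** Criterion 11 asks for the same factors at J0, M3, M6, M9 and M12. For cytokines, only J0 is a fixed draw. A responder's first-remission tube may fall on one of the later visits, but not on all of them and not on the same one for everybody.

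**The case against.** The case on the other side has several parts that stand.

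- **A reader might infer that the second value is taken at or after the outcome in everyone, and that all non-remitters are sampled at M24.** Neither follows. The outcome is status at M12. A patient first remitting at M6 or M9 is sampled before that assessment and may relapse by then. M24 is reserved for patients who never remit, and someone first remitting at M18 is sampled at M18.
- **The error rates rest on invented inputs.** Correct. The protocol gives no drift and no visit mix, and with zero drift the timing artefact disappears. The effect of remission itself would remain.
- **The method of analysis is assumed.** Section 12 describes none for objectives 10 and 11, and an analysis plan may. But criterion 10 does name the second value as a risk factor to be studied, so the problem is in the text as it stands.
- **A reader might conclude that the cytokine aim in Section 1.3 cannot be met.** There the TReg rise after rituximab is described with the remark "This increase is associated with IL-35 increase and PLA2R1-Ab decrease", and confirmation is assigned to an ancillary study whose analysis is not given. A comparison of J0 with the remission sample bears on that association. Other blood is drawn at fixed visits and retained at −80°C (Section 8.7), though its suitability for cytokines is not stated. Failure is not shown.
- **Moving the tube to M6 is no simple cure.** Under the mix assumed above, (25.6 × 0.65 + 14.4 × 0.35)/40 = 54% of M12 remitters have already remitted by M6. Patients untreated before M6 have no time since infusion at that visit.

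**Conclusion.** The concern holds for the second cytokine sample in criterion 10. Its timing is set by whether and when remission occurs, so an association with M12 remission cannot be read as prediction. How misleading the result would be is unknown: from no excess false positives if the cytokine is stable over time and unaffected by remission, through 9% to 21% at drifts of 0.25 to 0.5 SD over 24 months, to about 60% at 1 SD. All of these depend on assumed drifts and visit patterns and are illustrations only.

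The mismatch between criterion 11 and the schedule is a plain inconsistency that needs no assumption.

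The documents do not support going further. The J0 level is a valid baseline predictor, the remission sample has descriptive value, and the primary endpoint, the sample size and the safety evaluation are untouched. This is an inexpensive correction to a secondary objective.

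**What to change.** 1. In Section 3, criterion 10, name only the J0 cytokine level as a risk factor for remission at M12. Describe the first-remission or M24 sample as a descriptive correlate of remission.
2. In criterion 11, limit cytokines to the times the schedule collects, and state that the M3, M6, M9 and M12 list applies to the other factors.

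Both are wording changes; no tube is added or moved. The price is that there is no post-baseline cytokine predictor of remission. If the sponsor wants one, it needs a draw at a fixed visit before the outcome, analysed only in patients not yet in remission at that visit and taking account of time since rituximab. That would be an extra tube if the remission sample is also kept. It is optional and separate from the correction above.

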#### **M6 visit = 6 months after randomization +/-15 days**

- Consultation date
- Clinical examination: weight, blood pressure, edema
- Serious adverse events
- Changes in concomitant treatments
- Blood and urine lab results
- Estimated GFR CKD EPI
- Centralized assays for both arms:
  - 2 dry tubes of 5 ml of blood and 2 EDTA tubes of 3 ml of blood will be shipped to Nice at room temperature for PLA2R1-Ab, epitope profile determination, serum rituximab levels, anti-rituximab antibodies, and, B and T cells counts (see manual lab)
- **In the GEMRITUX arm**
  - If disease still active (UPCR remains > 3.5 g/g and albuminemia < 30 g/l): plan two 375 mg/m^2 Rituximab infusions at 1-week interval (+/- 2 days) between 5 and 14 days after M6 visit.
  - If remission (partial or complete, see p.12): symptomatic treatment to be continued.
- **In the personalized arm/ Patients who received RTX at M0**
  - If remission (partial or complete, see p.12): symptomatic treatment to be continued alone and contraception will be required during 12 months after the end of the treatment.
  - If disease still active / Restricted anti-CysR activity: plan two 375 mg/m^2 rituximab infusions at 1-week interval (+/- 2 days) between 5 and 14 days after M6 visit.

- if disease still active / Anti-CTLD1/7 activity: plan two 1g rituximab infusions at 2-week interval (+/- 2 days) between 5 and 14 days after M6 visit. For patient who will develop anti-rituximab antibodies, treatment with human anti-CD20 is widely recommended.

*NB: If the patient still active disease / anti-PLA2R1 Ab-; the symptomatic treatment should be optimized*

- **In the personalized arm/ Patients who received 6-month symptomatic treatment**

- If remission (partial or complete, see p.12): symptomatic treatment to be continued
- If disease still active / Restricted anti-CysR activity: plan two 375 mg/m^2 rituximab infusions at 1-week interval between 5 and 14 days after M6 visit.
- if disease still active / Anti-CTLD1/7 activity: plan two 1g rituximab infusions at 2-week interval between 5 and 14 days after M6 visit.

**For all:** plan M9 +/-15 days and hand out a prescription to the patient for blood and urine analyses\*

\* Blood sample: urea, creatinine, electrolytes (sodium, potassium, chloride, bicarbonate), protein, albumin, full blood count.

Spot morning urine sample: protein, albumin, urea, creatinine.

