### **M18 visit = 18 months after randomization +/-15 days**

- Consultation date
- Clinical examination: weight, blood pressure, edema
- Serious adverse events
- Changes in concomitant treatments
- Blood and urine lab results
- Estimated GFR CKD EPI
- Check remission status:
  - Complete clinical remission: urinary protein/creatinine ratio (UPCR) < 0.3 g/g in spot morning urine samples and Normal serum albumin and eGFR > 60 ml/min/1.73 m^2
  - Partial clinical remission: UPCR < 3.5 g/g with a decrease greater than 50% from baseline and improvement or normalization of the serum albumin concentration and increase of serum creatinine lower than 20%
- Centralized assays for both arms:
  - 2 dry tubes of 5 ml of blood and 2 EDTA tubes of 3 ml of blood will be shipped to Nice at room temperature for PLA2R1-Ab, epitope profile determination, B and T cells counts (see manual labPlan visit M24 +/-15 days and hand out a prescription to the patient for blood and urine analyses\*)

\*Blood sample: urea, creatinine, electrolytes (sodium, potassium, chloride, bicarbonate), protein, albumin, full blood count.

Spot morning urine sample: protein, albumin, urea, creatinine.

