### Schedule of assessments

|                                          | M0 | M3                                | M6 | M9 | M12 | M18 | M24 |
|------------------------------------------|----|-----------------------------------|----|----|-----|-----|-----|
| Selection criteria                       | X  |                                   |    |    |     |     |     |
| Informed Consent                         | X  |                                   |    |    |     |     |     |
| Pregnancy test                           | X  | X                                 | X  | X  | X   |     |     |
| Randomisation                            | X  |                                   |    |    |     |     |     |
| Medical history and demographics         | X  |                                   |    |    |     |     |     |
| Weight, Edema, Blood pressure            | X  | X                                 | X  | X  | X   | X   | X   |
| Vaccination                              | X  |                                   |    |    |     |     |     |
| HBP Medications                          | X  | X                                 | X  | X  | X   | X   | X   |
| Serious adverse events treatment related | X  | X                                 | X  | X  | X   | X   | X   |
| Estimated GFR CKD EPI                    |    |                                   | X  | X  | X   | X   | X   |
| Urine analyses                           | X  | X                                 | X  | X  | X   | X   | X   |
| Blood sample b                | X  | X                                 | X  | X  | X   | X   | X   |
| PLA2R1-Ab                                | X  | X                                 | X  | X  | X   | X   | X   |
| Epitope Profile                          | X  | X                                 | X  | X  | X   | X   | X   |
| Residual Rituximabemia                   |    | X                                 | X  | X  | X   |     |     |
| Rituximab-Ab                             | X  | X                                 | X  | X  | X   |     |     |
| Cytokine profile                         | X  | X At first remission a |    |    |     |     |     |
| B and T cells count                      | X  | X                                 | X  | X  | X   | X   | X   |
| End of study                             |    |                                   |    |    |     |     | X   |

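### The month 9 and month 12 post-infusion relapse predictors in criterion 11 are complete before the relapse window only in personalized-arm patients infused at M0

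*Protocol*

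**What the plan says.** Objective 11 (section 2.2) is "To determine risk factors for relapse (between M12 and M24) in patient responders at M12, pooled from the two arms". Section 3, criterion 11 sets the outcome: "Relapse is defined by an increased proteinuria > 3.5 g/g after remission at M12". It refers back to the markers of criterion 10, of which lymphocyte counts, rituximab level and neutralizing anti-rituximab antibodies are timed from infusion, and adds: "The risk factors studied will be the same as above measured at J0, M3, M6, M9 and M12 post-rituximab infusion".

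Section 8.5 times the M6 to M24 visits from randomisation, each within 15 days, with no visit between M12 and M18. Treatment starts at two different times:

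- Personalized patients with CTLD1/7 activity at M0 start 5 to 14 days after randomisation.
- Controls still active at M6, and personalized patients who had symptomatic treatment only and are still active at M6, start "between 5 and 14 days after M6 visit".

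The M18 central assays are "PLA2R1-Ab, epitope profile determination, B and T cells counts". In the Schedule of assessments, the "Residual Rituximabemia" row is marked at M3, M6, M9 and M12 only. The anti-rituximab antibody row is marked from M0 to M12, and B and T cell counts at every visit.

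**The concern.** A predictor of relapse between M12 and M24 has to be measured, and measured before the relapse is observed. Criterion 11 places its predictors on an infusion clock while samples are drawn on a randomisation clock. The two clocks agree for patients infused at M0 and differ by about six months for patients first infused after M6.

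All patients infused at M0 are in the personalized arm, and no control can be infused before M6. Whether the two latest predictors exist, and whether they precede the outcome, therefore depends on arm and on epitope profile at entry, in an analysis that pools the arms. Two problems follow:

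- A model that uses these time points drops every treated control through missing values.
- If M18 cell counts are used instead, markers taken during a relapse in some patients are treated as equivalent to markers taken before it in others.

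**Working it through.** **Step 1: place each post-infusion time on the visit grid.** Calendar time = start visit (0 or 6 months) + 5 to 14 days (0.16 to 0.46 month at 30.44 days per month) + offset. Visit windows are ±15 days (±0.49 month).

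| Time after first infusion | Infused after M0: month (visit) | Infused after M6: month (visit) |
|---|---|---|
| J0 | 0.2–0.5 (M0) | 6.2–6.5 (M6) |
| M3 | 3.2–3.5 (M3) | 9.2–9.5 (M9) |
| M6 | 6.2–6.5 (M6) | 12.2–12.5 (M12) |
| M9 | 9.2–9.5 (M9) | 15.2–15.5 (none) |
| M12 | 12.2–12.5 (M12) | 18.2–18.5 (M18) |

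If the M6 visit uses its full window, month 9 post-infusion spans 14.7 to 16.0. The M12 window closes at 12.5 and the M18 window opens at 17.5, so no visit covers it.

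**Step 2: what is measured there.** At M18 cell counts are drawn, but not rituximab level or anti-rituximab antibodies. M18 is the first scheduled visit after M12, so a relapse found at M18 is found together with those counts. The counts precede only a relapse first found at M24.

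**Step 3: how many responders are affected.** The protocol gives no figure to reproduce. As an illustration, take 32 per arm (64/2, no losses) and the rates in sections 7.1 and 7.2.

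- Control responders: 0.45 × 32 = 14.4. Taking 10 to 21% of 32 as spontaneous (3.2 to 6.7) leaves 14.4 − 6.7 = 7.7 to 14.4 − 3.2 = 11.2 infused after M6.
- CysR-restricted personalized patients: 0.30 × 32 = 9.6, of whom 0.50 × 9.6 = 4.8 remit without infusion. The 40% after low-dose rituximab gives 0.40 × 4.8 = 1.9 if it applies to the remainder, or 0.40 × 9.6 = 3.8 if it applies to all.
- CTLD1/7 personalized responders infused at M0: 0.70 × 0.85 × 32 = 19.0.

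| Group | Low late-infused case | High late-infused case |
|---|---|---|
| First infused after M6 | 7.7 + 1.9 = 9.6 | 11.2 + 3.8 = 15.0 |
| Infused at M0 | 19.0 | 19.0 |
| Never infused | 6.7 + 4.8 = 11.5 | 3.2 + 4.8 = 8.0 |
| All M12 responders | about 40 | about 42 |

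Late-infused patients are thus 9.6/40 = 24% to 15.0/42 = 36% of all responders. Among infused responders they are 9.6/28.6 = 34% to 15.0/34.0 = 44%.

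**Step 4: limits of the count.** The 19 is an upper bound on patients with an unambiguous clock. The 85% rate in section 7.1 is for repeated high-dose pulses, section 8.5 allows re-infusion after M6, and criterion 11 does not say which infusion starts the clock. The 8.0 to 11.5 never-infused responders have no post-infusion time at all.

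**The case against.** The strongest defence is that three of the five time points work. For late-infused patients J0, M3 and M6 post-infusion fall at the M6, M9 and M12 visits, where cell counts, rituximab level and anti-rituximab antibodies are all drawn. This stands, and it confines the problem to M9 and M12 post-infusion.

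A reader might infer that the aim in section 1.4, linking anti-rituximab antibodies to recurrence, is lost. The documents do not support that. Section 1.4 places the aim in an ancillary study and sets those antibodies at months 3 and 6, which are sampled in both arms. A reader might also infer that M18 markers are useless for predicting relapse, or that no antibody is assayed there. Neither holds: M18 cell counts can precede a relapse first seen at M24, and PLA2R1 antibodies are measured at M18. Only anti-rituximab antibodies and drug level are absent.

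A milder reading is that the list was meant as study visits. It matches the anti-rituximab antibody row of the schedule, and section 8.4 loosely describes the visits as post-treatment. That is possible, but criterion 11 then names the wrong clock and still needs correcting.

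Finally, reverse causation arises only if post-M12 values enter the model, and a statistical analysis plan could exclude them. That is fair as to the model. The time points themselves are fixed in the protocol, though, and no later plan can analyse a month 15 sample that was never scheduled.

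**Conclusion.** The point holds for M9 and M12 post-infusion only. In patients first infused after M6, the month 9 value is never sampled. The month 12 value consists of cell counts without rituximab level or anti-rituximab antibodies, and these counts are usable at most for relapse first found at M24. Complete values before the relapse window exist only for personalized-arm patients infused at M0. At these two time points the pooled analysis is confounded with arm and open to reverse causation.

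The size is roughly 10 to 15 of about 40 to 42 expected M12 responders. This rests on 32 per arm, no losses, the protocol's planning rates, and its 10 to 21% one-year spontaneous remission rate applied to controls. The timing argument depends on none of these. It would be too strong to say that the whole relapse analysis becomes a one-arm analysis, because the J0, M3 and M6 post-infusion predictors remain available in both arms.

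**What to change.** Amend criterion 11 as follows:

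- Make M12 after randomisation the landmark, and admit as predictors of later relapse only markers measured at or before the M12 visit.
- For infusion-timed markers (rituximab level, anti-rituximab antibodies, cell counts), use J0, M3 and M6 post-infusion, with drug level naturally starting at M3. Alternatively or additionally, use the M12-visit value adjusted for infusion history (none, M0, M6, both).
- State which infusion starts the clock for patients treated at both M0 and M6.
- Treat never-infused responders as a separate category.

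Moving every predictor to the randomisation clock would be simpler but is not free. M3 and M6 rituximab levels would be zero by design in every control and would act as a marker of arm, and time since last infusion is undefined for never-infused responders.

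The cost is a short change to section 3 and to the matching analysis. No new samples or visits are needed. The downside is that M9 and M12 post-infusion values are dropped as infusion-clock predictors.
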